##### **Perinatal Anxiety Screening Questionnaire (PASQ)** [117]

The PASQ is a newly constructed screening tool, created by our study team specifically for perinatal AD screening [117]. The PASQ screens for all core AD (PD, SAD, SP, GAD, AG, separation anxiety), as well as OCD and PTSD. The tool includes 8 primary “yes/no” questions to probe for the core feature of each AD (e.g., “Do you worry a lot about many different things [e.g., your pregnancy or baby, parenting ability, family finances, work or school, or world events]?”). For each AD, if the participant selects “yes” to the primary question, the next question for that AD section is asked. However, if the participant selects “no” to the primary question, they will move to the next AD section and will be asked a new “yes/no” primary question for a new AD. The PASQ has a total of 36 possible questions, and the number of questions for each AD section varies depending on the number needed to effectively address the core DSM-5 diagnostic criteria of each AD. There are 3 possible questions for SP, 6 for PTSD, 7 for OCD and the remaining AD sections (SAD, PD, AG, GAD, separation anxiety) all have 4 possible questions each. This tool was created for the current project to include examples and descriptions catered to new and expectant parents.

#### Additional measures

##### Insomnia Severity Index (ISI)

The ISI is a 7-item, self-report measure of sleep difficulties experienced over the previous two weeks [118]. Items are rated on 0–4, Likert-type scales with 0 representing an absence of symptoms, and 4 representing severe symptoms. Items are summed to yield a total score, with higher scores representing more severe sleep difficulties. Scores between 15–21 indicate moderate insomnia, while scores over 22 indicate severe insomnia. In clinical samples, a cut-off of 15 has yielded a sensitivity of 78% and a specificity of 1.00 for detecting cases of insomnia [119]. Evidence of ISI validity has been demonstrated by moderate but significant correlations between ISI scores and both subjective (sleep diary) and objective (polysomnography) measures of sleep [119]. Similarly, the ISI has shown sustained sensitivity to changes in sleep difficulties over time, with total scores being paralleled by sleep diary data, polysomnography and clinician evaluation [118]. This measure has shown excellent internal consistency in clinical and community samples (Cronbach alphas from 0.73—0.91), and has been deemed a reliable tool to measure insomnia severity [118, 119].

##### Family Work Quality Questionnaire (FWQQ)

The FWQQ, developed by Janzen and Hellsten [120] is a 28-item self-report measure of unpaid family work. This measure assesses five subscales of unpaid work quality: demands (time pressure and differing demands); equity (fairness in the division of unpaid work); autonomy (freedom over types of work conducted and decision); social resources (assistance from family and friends); caregiving reward (gratification received from responsibilities). Items within each subscale are rated on a 4-point Likert scale from 1 (strongly disagree), to 4 (strongly agree). The scale has shown adequate internal consistency, with Cronbach alphas ranging from 0.75-0.88 [120].

##### Lab based measures

Questions pertaining to participant demographic information, identity, experiences, reproductive history, current pregnancy and birth, childcare distribution, relationship and sexual satisfaction, postpartum mental health service utilization and covid-19 were developed by our research team and included in the study questionnaires. Much of this content has been used before in previous studies [46, 121, 122].

##### Demographic information

Our team has well-established questions pertaining to participant demographic information which we have used in multiple studies [46, 121, 122]. Demographic characteristics assessed include age, relationship status, race/ethnicity, household income, income needs, education, employment status, geographical area of residence.

##### Identity

Questions to better understand participants’ identity, including sex assigned at birth, gender, pronouns, sexual orientation, belonging to a minority community have been included. Additionally, participants are asked if they have experienced discrimination during their medical care due to their identity or an experience (e.g., race, social class, religion, weight/body size, chronic illness, history of substance use).

##### Reproductive, pregnancy and birthing information

Our team has well-established questions pertaining to participant reproductive history, current/most recent pregnancy, and birth [46, 121, 122]. Information collected includes parity, delivery, number of children (biological, non-biological), reproductive loss, conception, birth plan, mode and location of delivery, birth weight, neonatal health, infant feeding, infant sleep arrangement.

##### Domestic labour

We are also collecting information pertaining to domestic labour. Questions ask about the participant’s parenting/living situation, parental leave, childcare, share of care of children and share of domestic responsibilities.

##### Satisfaction

Relationship satisfaction, sexual satisfaction, and irritation and/or anger with the division of childcare and domestic chores were each asked about via a single question. Relationship satisfaction was rated on a 4-point Likert scale ranging from “Very dissatisfied” to “Very satisfied.” For sexual satisfaction, participants are asked to select a response ranging from “Dissatisfied” to “Satisfied,” with an additional option to select “I choose not to answer.” The irritation and/or anger with the division of childcare and domestic chores was rated on a 5-point Likert scale ranging from “Not at all” to “Extremely.”

##### Postpartum mental health

In the postpartum questionnaire, participants are asked to provide information regarding their engagement with mental health services. Specifically, they are asked if they have sought any mental health assessment(s) since their prenatal interview with us. If an assessment for mental health difficulties was sought, they are then asked if they experienced any barriers (e.g., cost, location, race or culture, time, etc.). If they received an assessment, they are asked additional questions about diagnosis and treatment (e.g., which, if any diagnoses were assigned, what, if any, treatment(s) they are receiving, how this treatment is funded and what practitioner provides this treatment if applicable).

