### Objectives

The core objective of this research is to identify one or more accurate screening tools to detect perinatal AD. To this end, we will:Assess the accuracy of a range of screening tools for perinatal AD as a whole and individually. Specifically, we will report the full composite of screening tool metrics for each evaluated measure:i)at each assessment point (prenatal and postpartum);ii)for the core DSM-5 anxiety disorders alone, and including OCD and PTSD;iii)for each of the individual AD; andiv)across parity (parity = 0, parity ≥ 1) and major ethnic groups.Based on the above, we will report the most accurate screening tool for the AD as a group, and for each individual AD.

Secondary and exploratory study objectives:Document the prevalence of perinatal AD in pregnancy and the postpartum. As this study requires an unselected/representative sample of perinatal people from within a specified geographical region, it provides the opportunity for us to document prevalence.Explore relationships between participant demographic characteristics (e.g., age, relationship status, race/ethnicity, household income, income needs, education, employment status, geographical area of residence), identity (gender, sexual orientation), experiences with discrimination (e.g., race, social class, religion, weight/body size, chronic illness, history of substance use), and sleep with AD.Assess perinatal people’s experience with mental health assessment and treatment seeking and utilization. Among participants who reported symptoms meeting criteria for one or more AD, we will assess assessment and treatment seeking as well as any barriers experienced (e.g., cost, location, race or culture, time, etc.). Among those who received an assessment or treatment, we will ask about the nature, duration, and costs associated with any assessments or treatment received, as well as diagnoses obtained, and practitioner type.Assess the relationship between unpaid domestic labour (i.e., household chores and childcare responsibilities) and mental health and relationship satisfaction. Specifically, we will assess the overall burden (i.e., quantity), perceptions of fairness, and gender distribution of unpaid domestic labour with respect to mental health and relationship satisfaction prenatally and postpartum.

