#### Ethical and safety considerations

At the start and end of each questionnaire, all participants are provided with a list of pregnancy and postpartum-related resources in their community. During study interviews, any participant who reports clinically significant symptoms, or symptoms meeting diagnostic criteria for one or more AD, are provided a list of treatment services in their community, as well as individualized referral suggestions from the study interviewer.

If it is determined that a participant is suffering from suicidal ideation, additional steps are taken to ensure participant safety. If a participant endorses suicidal ideation during the completion of the online questionnaire (i.e., answers ‘Yes, quite often,’ or ‘Sometimes,’ to: “The thought of harming myself has occurred to me.”) on the measure administered to assess depressed mood (i.e., the Edinburgh Perinatal Depression Scale) [43], an additional risk assessment questionnaire then probes for suicidal behaviour. If a participant is deemed to have elevated risk for suicidal behaviour, the study team is alerted, and the participant is contacted via phone by a trained team member within 24 hours. If no contact is made, a follow up email is sent to maximize earliest participant contact. If suicidal ideation is identified during a study interview, the interviewer takes the necessary steps to ensure the participant’s safety. Management of suicidal ideation is based on the study safety and emergency mental health protocol.

In the event of a perinatal loss, participants are contacted by a member of the study team to express support, and perinatal loss specific resources are provided if desired with the option for additional support or resources at a later time, if needed. Only data provided prior to a perinatal loss will be retained in the data set (e.g., in the event that a loss occurs following the completion of the prenatal questionnaires and interview, data will be retained).

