### Assessment tools

See Table 1 for a summary of study measures.

**Table 1 Tab1:** Summary of study measures

Domain	Measure	Method	Location
*Intake*			
Consent			Online
*Prenatal Questionnaire (16–32 weeks’ gestation)*			
Characteristics	Demographic and reproductive history information	Self-report	Online
AD Screening Measures	Perinatal Anxiety Screening Scale (PASS) State-Trait Anxiety Inventory (STAI-Y2) Edinburgh Postnatal Depression Scale (EPDS) Kessler Psychological Distress Scale (K6/K10) Matthey Generic Mood Questionnaire (MGMQ) Antenatal Risk Questionnaire (ANRQ-2A) Generalized Anxiety Disorder (GAD-7) Anxiety Disorders 22 (AD-22) Perinatal Anxiety Screening Questionnaire (PASQ)	Self-report	Online
Other functioning	Insomnia Severity Index (ISI) Covid-19 experience Family Work Quality Questionnaire (FWQQ)	Self-report	Online
*Prenatal Interview (2-4 weeks after prenatal questionnaire completion)*			
Diagnosis and onset (ADs, OCD, PTSD)	Diagnostic Assessment Research Tool (DART for DSM-5-TR)	Diagnostic Interview	Zoom or phone
*Pregnancy Check-In*			
Characteristics	Pregnancy status and birth date	Self-report	Online
*Postpartum Questionnaire (6–16 weeks postpartum)*			
Characteristics	Birthing information	Self-report	Online
AD Screening Measures	Perinatal Anxiety Screening Scale (PASS) State-Trait Anxiety Inventory (STAI-Y2) Edinburgh Postnatal Depression Scale (EPDS) Kessler Psychological Distress Scale (K6/K10) Matthey Generic Mood Questionnaire (MGMQ) Antenatal Risk Questionnaire (ANRQ-2A) Generalized Anxiety Disorder (GAD-7) Anxiety Disorders 22 (AD-22) Perinatal Anxiety Screening Questionnaire (PASQ)	Self-report	Online
Other functioning	Insomnia Severity Index (ISI) Covid-19 experience Family Work Quality Questionnaire (FWQQ) Mental health support seeking	Self-report	Online
*Postpartum* *Interview* *(2-4 weeks after prenatal questionnaire completion*)			
Diagnosis and onset (ADs, OCD, PTSD)	Diagnostic Assessment Research Tool (DART for DSM-5-TR)	Diagnostic Interview	Zoom or phone

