The study includes a number of additional methodological strengths. Specifically, the study is powered to ensure we can assess the accuracy of included screening tools both for the AD as a whole, but also for each individual AD. Our approach to recruitment is designed to result in data for 1,000 pregnant and 1,000 postpartum people. We are over-sampling, where needed, perinatal people with specific AD so that we are able to report on screening accuracy for each of the individual AD.

Beyond the core goal of this research (i.e., to assess the accuracy of various self-report measures when used as screening tools for perinatal AD), we have the opportunity to explore a number of additional research questions. For example, because this research is based on DSM-5 anxiety and related disorders, we are also able to explore screening for separation anxiety disorder. To our knowledge, no findings related to screening for adult separation anxiety among perinatal people have been published. In addition to providing information about screening accuracy for adult separation anxiety disorder, we will also be able to provide the first estimate of the prevalence and incidence of this condition among perinatal people. Further, we will document the point prevalence and postpartum incidence of perinatal AD in pregnancy and the postpartum. To our knowledge, perinatal AD prevalence, based on DSM-5 criteria has yet to be reported. Further, we will be able to assess the extent to which participants who report symptoms meeting criteria for one or more AD go on to receive an assessment and treatment for these conditions. We will also assess various predictors (e.g., demographic, reproductive, identity, experience of discrimination) of perinatal AD symptoms and diagnosis, as well as assessment and treatment access and utilization. Finally, we will assess the relationship between the burden and gender distribution of unpaid domestic labour (i.e., household chores and childcare responsibilities) and mental health.

Findings from this research will provide rich data to answer not only our core research questions but additional, important questions pertaining to perinatal AD.

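### Help-seeking is measured once, from the study's own interview onward, by an item that can miss care in progress and ends before the postpartum diagnosis

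*Protocol article*

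**What the plan says.** The Objectives section lists, among the secondary and exploratory aims, help-seeking and use of care: "Among participants who reported symptoms meeting criteria for one or more AD, we will assess assessment and treatment seeking as well as any barriers experienced". The Discussion says the study will show "the extent to which participants who report symptoms meeting criteria for one or more AD go on to receive an assessment and treatment".

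The item itself is described under Postpartum mental health. In the postpartum questionnaire participants "they are asked if they have sought any mental health assessment(s) since their prenatal interview with us". The treatment questions depend on the answer: "If they received an assessment, they are asked additional questions about diagnosis and treatment". Table 1 lists "Mental health support seeking" under the postpartum questionnaire and not under the prenatal one.

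Ethical and safety considerations describes what happens at each study interview: "any participant who reports clinically significant symptoms, or symptoms meeting diagnostic criteria for one or more AD, are provided a list of treatment services", with individual referral suggestions from the interviewer. Every participant also receives a resource list at the start and end of each questionnaire. Procedures places each interview 2 to 6 weeks after its questionnaire.

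**The concern.** The objective concerns seeking and use of care among people with an AD. The single item looks back only as far as the study's prenatal interview, and treatment is reached only through a newly sought assessment. Three things follow from collecting the data this way, and a later analysis plan could not repair them.

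- Care that began before the prenatal interview, and is still going on, can go unrecorded.
- For AD found prenatally, the observation period opens at the moment the study supplies a diagnostic interview and a referral.
- The item is answered before the postpartum diagnosis, so nothing is seen after it.

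At stake is a descriptive result that could be read as the share of people with a perinatal AD who receive care, when the item measures something narrower and different for different participants.

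**Working it through.** No sample size or power figure attaches to this point and the article states no figure to reproduce. The check sets the sections side by side and adds timeline arithmetic.

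**Could another instrument fill the gap?** The diagnostic interview is described as covering diagnosis, age of onset and relation to reproduction, not care. The full antenatal risk questionnaire has a domain on treatment received, but the study lists only its two anxiety items. The Abstract names treatment utilization among the questionnaire content without a time point. No described prenatal item asks about care.

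**Four kinds of participant, followed through the item as written:**

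1. *Assessed before the prenatal interview, still in treatment, no new assessment.* The truthful answer to the lead question is no, and the treatment questions are skipped. No care is recorded.
2. *AD present at the prenatal interview.* Referral is given at the start of the recall period, so all recorded seeking follows study assessment and referral. No unreferred group with prenatal AD exists for comparison.
3. *No clinically significant symptoms at the prenatal interview, AD beginning before the postpartum questionnaire.* No individual referral was given. Seeking up to the questionnaire is captured; seeking after it is not.
4. *AD first identified at the postpartum interview (this includes group 3).* The item was answered 2 to 6 weeks earlier, and no later help-seeking measure is described. Care after the diagnosis is unobserved.

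**Timeline.** Inputs from Procedures: prenatal questionnaire at 16 to 32 weeks' gestation, postpartum questionnaire at 6 to 16 weeks, interview lag 2 to 6 weeks. Birth at 40 weeks is an assumption.

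- Prenatal interview: 16 + 2 = 18 to 32 + 6 = 38 weeks' gestation.
- Recall length = (40 − interview week) + postpartum questionnaire week.
- Shortest: (40 − 38) + 6 = 8 weeks. Longest: (40 − 18) + 16 = 38 weeks. Ratio 38/8 = 4.75.
- Table 1 gives a lag of 2 to 4 weeks. The latest prenatal interview is then at 32 + 4 = 36 weeks, the shortest recall (40 − 36) + 6 = 10 weeks, and the ratio 38/10 = 3.8.
- Postpartum diagnosis: 6 + 2 = 8 to 16 + 6 = 22 weeks postpartum by Procedures.

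These are extremes and not a typical spread, but on either lag the recall period differs greatly between participants.

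**Numbers affected.** With the Abstract's prevalence of about 20% and 1,000 prenatal interviews, 0.20 × 1,000 = 200 people would be in group 2. The article does not give the share of postpartum cases that are new. If 10% to 40% of about 200 were new (an assumption for illustration), 20 to 80 people would be in group 4. The number in group 1 cannot be derived from the article.

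**The case against.** The strongest reply is that the article claims little. A reader might infer that the item is meant to estimate usual access to care, or whether people find care unprompted. The documents do not support that reading: no section promises it, and the statements that AD go undetected or untreated are background that does not rest on this item. For AD found prenatally, a recall period starting at that interview suits a question about what happens next. This stands, and what remains for these cases is how the result is labelled.

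A reader might also infer that nothing useful is learned about new postpartum cases, or that everyone in the denominator was referred. That goes too far. Individual referral depends on symptoms or an AD at a study interview, so people who were well prenatally had none. Their seeking before the questionnaire is captured and is closer to unprompted, although they too received resource lists and an interview. Limiting the analysis to prenatal AD would discard this informative group.

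Third, the article is condensed and the questionnaires are not shown. Objectives mentions duration and costs, which the item description does not list, so the description is not exhaustive. A prenatal item could exist. Against that, Table 1 and the section on lab-based measures both place service use postpartum, and the stated recall period and gating are explicit. Nor does the article give a scoring rule that counts a person already in treatment as not seeking care; the point is that, as described, no data would be collected to show otherwise.

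Finally, the objective is secondary, and the share of new cases is not a document figure. Both are accepted.

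**Conclusion.** The concern holds in limited form. As described, the item can record a person already in treatment as having no care. It shows only post-referral seeking for AD found prenatally, and nothing after diagnosis for AD first found postpartum. The Discussion's statement, "we will be able to assess the extent to which participants who report symptoms meeting criteria for one or more AD go on to receive" care, is therefore unsupported for the last group.

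The direction of any net bias is unknown. Study referral may raise recorded seeking and missed ongoing care lowers it, and the data collected do not separate the two. About 200 people fall in the referred group if prevalence is 20% of 1,000. Recall differs between participants by a factor of 3.8 to 4.75 at the extremes, depending on which stated lag applies and assuming birth at 40 weeks. The core objective, screening accuracy, is untouched. The conclusion rests on the article describing the timing and gating of the item correctly.

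**What to change.** 1. For participants still to be assessed, add short items to the prenatal questionnaire on assessment and treatment before that point, including treatment in progress. Ask the postpartum treatment questions of everyone, not only of those newly assessed.
2. Report the postpartum item in two groups: AD present at the prenatal interview, labelled as uptake after study assessment and referral; and AD first found postpartum, labelled as care sought before diagnosis. Take account of length of recall in both.
3. Narrow the Discussion so that later receipt of care is claimed only for AD identified prenatally.

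The cost is a few REDCap items and some wording. The downside is that pre-interview data come only from the later part of the cohort. Against the recruitment target of 1,200, Current status gives two enrolment counts, leaving 1,200 − 783 = 417 or 1,200 − 727 = 473 still to enrol at the time of writing. The postpartum change could reach more people, at most 1,200 − 316 = 884 before attrition, since 316 had completed the study. Collection was due to end in January 2025, so the number actually reachable depends on when the change is made. Items 2 and 3 can be done for the whole cohort at any time.
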